***Foetal heart monitoring in low-income countries*: *clinical observations.***

**Scientific Abstract**

Almost all (>98%) perinatal deaths occur in low- and middle-income countries (LMIC) and are related to suboptimal care and obstetric complications. Intrapartum-related complications account for a large proportion of neonatal death and childhood morbidity. The lack of skilled human resources in health care is a crucial bottleneck for the scale up of (cost-) effective evidence-based interventions to reduce perinatal mortality in low-income countries (LIC). [1-7].

This project will commence in the only referral hospital in Zanzibar, Tanzania. The aims of the overall project are to find novel strategies of intrapartum care in low resourced settings (ethical approval no: ZAMREC/0002/May/016).

The systematic review on *strategies and implementation of intrapartum foetal surveillance in LMIC* (registered on PROSPERO, CRD42016038679), provides an overview of the available literature on FCM in this setting. This part of the research project consists of two aims: a baseline assessment of quality of intrapartum care and a preparation for an analysis of the record keeping. This allows us to compare the intrapartum care via a criteria based audit in which current practice will be compared with local guidelines. The analysis of record keeping could determine the extent to which the records can be reliably used to assess quality of care in future studies.

**Plan of Investigation: Clinical observations and record keeping**

**Objectives**

1. To conduct and observational study to assess the current methods used for foetal and contraction monitoring (FCM) during labour.
2. To perform a criteria based audit to determine the adherence to current established MMH guidelines, and assess factors that influence adherence.
3. To determine challenges faced at MMH in FCM
4. To prepare for a validation study between observations and record books. (In addition to later compare this to previously analysed record keeping at the MMH in 2015.)

**Selection of labours**

Observations will be held at the maternity ward of MMH. At least 150 labours will be observed, maximum 8 labours per one shift. This corresponds to the shifts of the midwifes: morning shift: 7.30 am till 2.30pm, afternoon shift: from 2.30 pm till 8.30 pm and night shift: 8.30 pm till 7.30 am. Even though a labour exceeds the shift, observations will be continued until delivery. A schedule of which shift to incorporate will be created in advance in order to shadow as many midwives as possible, with different levels of experience. Labours will be selected based on the following criteria: the first women to reach active phase who meets the inclusion criteria and is either being admitted or already at the ward. The inclusion of labours will be both high- and low-risk (as determined antenatally or on admission), both nulli- and multipara. High-risk pregnancies are defined as women with a previous caesarean section, induced labour by oxytocin or having pregnancy, medical complications (preterm and postterm labours, PROM, meconium, maternal illness, severe bleeding, foetal distress (Intrauterine foetal death, IUFD), poor progress (crossed alert line of the partogram), severe hypertensive disorder, fever or other infections). Key events are defined as: maternal bleeding, temperature measurement (fever), fits, bleeding, caesarean section (CS), intra-uterine resuscitation, fluids etc. A labour will be observed once the woman reaches active phase of labour (4 cm cervical dilatation) until complete delivery of the baby (independent on whether the cervical dilatation is reached at admission or during intra-facility care). In case of an IUFD detected during labour, observations will be stopped, but data will be included in the results. Exclusion criteria for labour**:** woman for elective CS, diagnosed with IUD by staff before admission by ultrasound (US) or women who are send for immediate CS upon arrival. An information sheet in Kiswahili and a verbal explanation by a midwife in Kiswahili will be provided to the labouring women on the aim of this study: observing staff taking care of her. Informed consent will be asked from the labouring women (on arrival) and from the staff as a group (once study commences one time). Staff can tell upfront in case they do not want to participate. As an observer, my job is to observe the intrapartum care and I am not expected to intervene.

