**Data analysis**

PartoMa guidelines will be used to assess whether FCM was done according to the standards set of criteria we have assessed. The relevant criteria are described in the PartoMa guidelines. The influence of the following factors on adherence will be assessed: low-vs high-risk pregnancies, experienced vs non-experienced (self-identified), midwives or doctors, nulli- vs multipara, morning vs afternoon vs night shifts, occurrence of key vs non key events will be calculated:

1. Participant characteristics will be descriptively presented using means and standard deviations for continuous variables and frequencies and percentages for categorical variables.
2. FHM adherence according to standard will be calculated:
   - Percentage of number of labours that completely adhered to guidelines (dichotomized outcome, yes/no) for the following 3 groups: heart rate monitoring, contraction monitoring and both.
   - Score of FHM adherence, defined as: (number of observations) / (number of expected observations given the duration of labour).
   - Score of contraction monitoring adherence, defined as: (number of observations) / (number of expected observations given the duration of labour).
   - Score of maternal pulse adherence, defined as: (number of observations) / (number of expected observations given the duration of labour
   - Average interval between observations: average in minutes and standard deviation
3. Influence of low-vs high-risk pregnancies, experienced vs non-experienced midwives or doctors, nulli- vs multipara, morning vs afternoon vs night shifts, occurrence of key vs non key events on the FHM score will be assessed, using a Poisson distribution analysis.
4. Descriptive analysis of structural challenges and woman-to-staff contact.

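### The Poisson analysis of shift type and staff experience states no allowance for labours sharing a shift or staff, so run as written its standard errors for these two factors are too small

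*Protocol*

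**What the plan says.** Under Selection of labours, the unit scheduled is the shift. The protocol sets a minimum number of labours and a ceiling per shift: "At least 150 labours will be observed, maximum 8 labours per one shift". Shifts are the midwives' working shifts, of three types ("This corresponds to the shifts of the midwifes: morning shift: 7.30 am till 2.30pm", then afternoon and night), and they are chosen ahead of time so that junior and senior staff are both covered: "A schedule of which shift to incorporate will be created in advance in order to shadow as many midwives as possible, with different levels of" […]. A labour may outlast its shift: "Even though a labour exceeds the shift, observations will be continued until delivery".

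Under Data analysis, item 2 defines one score per labour: "Score of FHM adherence, defined as: (number of observations) / (number of expected observations given the duration of labour". Item 3 lists the factors to be related to that score, among them "experienced vs non-experienced midwives or doctors, nulli- vs multipara, morning vs afternoon vs night shifts, occurrence of key vs non key events on the FHM" […], and says that their influence "will be assessed, using a Poisson distribution analysis". The text names no cluster term, random effect, robust variance or overdispersion term. It gives no ICC, planned number of shifts, number of midwives or mean number of labours per shift.

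**The concern.** Labours observed in one shift share staff, workload and ward conditions, so their scores are likely to be positively correlated. Shift type is constant across the labours taken from one shift, apart from those that run over. Staff experience follows the provider. For these two factors the information comes mainly from the number of shifts and providers, not from the number of labours. A plain Poisson model takes records as independent and sets the variance equal to the mean. Applied to this design, it can present chance differences between a few shifts or midwives as effects of time of day or of experience. Assessing what influences adherence is part of objective 2, so these comparisons belong to a stated aim.

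**Working it through.** The protocol gives no power, alpha, SD or ICC and no derivation of 150, so there is no figure of its own to reproduce. What follows sizes the problem under stated assumptions.

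**Inputs from the protocol.** N = 150 labours (minimum); m ≤ 8 labours per shift (a ceiling, not a mean). Minimum number of shifts: 150/8 = 18.75, so 19. With 3 per shift it would be 150/3 = 50.

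**Assumed inputs.** Two-sided alpha 0.05; ICC from 0.01 to 0.30; equal numbers of labours per shift, m = 8 or m = 3.

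**Formulas, for a factor that is constant within a shift.**
- Design effect: DE = 1 + (m − 1) × ICC
- Effective sample: 150/DE
- Factor by which the standard error is too small: √DE
- True type I error: 2 × [1 − Φ(1.96/√DE)]

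Example, m = 8 and ICC 0.10: DE = 1 + 7 × 0.10 = 1.70; 150/1.70 = 88; √1.70 = 1.30; 1.96/1.30 = 1.50, giving 13.3%.

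| Labours per shift | ICC | DE | Effective N | SE factor | Type I error |
|---|---|---|---|---|---|
| 8 | 0.01 | 1.07 | 140 | 1.03 | 5.8% |
| 8 | 0.05 | 1.35 | 111 | 1.16 | 9.2% |
| 8 | 0.10 | 1.70 | 88 | 1.30 | 13.3% |
| 8 | 0.20 | 2.40 | 62.5 | 1.55 | 20.6% |
| 8 | 0.30 | 3.10 | 48 | 1.76 | 26.6% |
| 3 | 0.01 | 1.02 | 147 | 1.01 | 5.2% |
| 3 | 0.05 | 1.10 | 136 | 1.05 | 6.2% |
| 3 | 0.10 | 1.20 | 125 | 1.10 | 7.4% |
| 3 | 0.30 | 1.60 | 94 | 1.26 | 12.1% |

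**Check by simulation.** Poisson regression with log(expected observations) as offset, 150 labours, a random shift effect on the log rate and no true effect of the factor. Assumed: about 13 expected observations per labour and a score of 0.4; 1,000 runs per setting.

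| SD of shift effect (log rate) | Approx. ICC | Shift-level factor, 8 per shift | Shift-level factor, 3 per shift | Labour-level factor, 8 per shift |
|---|---|---|---|---|
| 0 | 0 | 5.0% | 4.7% | 4.5% |
| 0.1 | 0.05 | 10.0% | 5.6% | 5.5% |
| 0.2 | 0.175 | 22.3% | 12.2% | 7.1% |
| 0.3 | 0.329 | 34.4% | 21.4% | 11.8% |

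At the larger SDs the simulated errors exceed what the design effect alone gives, because the shift effect also raises the total variance above the mean and a plain Poisson model cannot absorb that. At SD 0.2 the mean count is 0.4 × 13 = 5.2, and the added variance is 5.2² × (e^0.04 − 1) = 1.10. The variance-to-mean ratio is then 1 + 1.10/5.2 = 1.21, and DE = 1 + 7 × 0.175 = 2.225. Their product is 2.70, and 1.96/√2.70 = 1.19 gives about 23%, close to the simulated 22.3%.

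**Separating the two sources.** With no shift effect but labour-level variation of log-SD 0.3, a naive Poisson test already rejects about 10% of the time. Correcting overdispersion alone is not enough when shifts are full: with shift log-SD 0.15 to 0.3 and labour log-SD 0.3 to 0.5, a quasi-Poisson scale still left 8% to 23%. Shift-clustered errors with a t reference brought rejection to 4% to 8%.

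**The case against.** The strongest reply is that naming a Poisson distribution fixes a family, not a variance estimator. It is compatible with a random shift effect, GEE or robust errors, and such detail often sits in a statistical analysis plan, which is not shown. This stands in part. A reader might infer that labours will be analysed as independent, but the protocol does not say so; it only states no allowance. The point remains because the protocol does name its model, and the model as named does not match the sampling design described a page earlier. Part of the remedy, the identifiers, must also be in place when data are collected.

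A reader might also infer that the results would be far too optimistic. The documents do not support that. Eight is a ceiling, and the aim of shadowing many midwives favours more shifts with fewer labours in each. At ICC 0.01 with 8 per shift, or ICC 0.05 with 3 per shift, the error is about 6%. Large simulated errors also partly reflect labour-level overdispersion rather than shared shifts.

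Two further limits stand. The protocol promises no confidence intervals or p-values, and most of the planned output is descriptive, so it cannot be said that the adherence percentages will be reported too precisely; clustering by itself does not bias them. And the nesting is not strict: labours can cross shifts, and experience may differ between providers within a shift, so 19 is not necessarily the effective sample for experience.

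**Conclusion.** The point holds for shift type and staff experience: the Poisson analysis, run as written, gives standard errors that are too small for them. The direction needs only positive correlation within shifts or providers. The size is not determined by the protocol. By the design effect, type I error at a nominal 5% is about 6% to 27% with 8 labours per shift and 5% to 12% with 3, for ICC 0.01 to 0.30, and overdispersion between labours adds to it in a plain Poisson model. The ICC, the mean number of labours per shift and the alpha level are assumptions. Risk group, parity and key events vary within shifts and are less affected by clustering. This should be corrected, but it is not critical: the study is a single-hospital observational audit and the affected comparisons form part of one of four objectives.

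**What to change.** In Data analysis item 3, model the count of observations with log(expected observations) as offset, using one of:
- GEE or cluster-robust variance by observed shift, with a small-sample t correction because there may be only about 19 shifts; or
- a mixed Poisson model with random effects for shift and attending provider, cross-classified because labours can run past a shift.

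State how shift and experience are assigned to a labour that spans more than one shift or provider. Record a shift ID and a coded provider ID for each labour, if supplement 1 (not shown) does not already do so. Report the number of shifts and providers beside the number of labours, and use the same clustering for any interval placed on an adherence percentage.

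Cost: a few lines of analysis text, two data fields, slightly more analysis work and wider intervals.

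### The FHM score covers the whole labour but is related to shift and staff experience, which can change within a labour; one label per labour can misclassify exposure and will usually dilute these contrasts

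*Protocol*

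**What the plan says.** In the protocol, Selection of labours, the shifts are given as "morning shift: 7.30 am till 2.30pm, afternoon shift: from 2.30 pm till 8.30 pm and night shift: 8.30 pm till 7.30 am". The observation window is set by the labour and not by the shift: "A labour will be observed once the woman reaches active phase of labour (4 cm cervical dilatation) until complete delivery of the baby". The section adds: "Even though a labour exceeds the shift, observations will be continued until delivery". On numbers it says "At least 150 labours will be observed, maximum 8 labours per one shift".

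Data analysis, item 2, defines the outcome as "Score of FHM adherence, defined as: (number of observations) / (number of expected observations given the duration of labour". The denominator is the duration of the labour, not of a shift or of one person's attendance.

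Item 3 relates this score to several factors, among them "experienced vs non-experienced midwives or doctors, nulli- vs multipara, morning vs afternoon vs night shifts", and names the method: "morning vs afternoon vs night shifts, occurrence of key vs non key events on the FHM score will be assessed, using a Poisson distribution analysis". The lead-in to the section describes experience as "experienced vs non-experienced (self-identified), midwives or doctors", so it is a property of the staff member and not of the labour.

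No rule is given for placing a labour that crosses a shift change, or is attended by staff of differing experience, in one level of these factors. The Data collection tool section says that observations and key events are noted by shift as well as by labour. It refers to a supplement 1, which is not among the documents, for the data items.

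**The concern.** The outcome is fixed at labour level, while two of its explanatory factors can change part-way through a labour that is deliberately followed past hand-over. If each labour carries one shift label and one experience label, checks made or missed by the next shift count for or against the shift and staff on the label. That is misclassification of exposure, and its usual effect is to shrink the contrast.

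Objective 2 includes finding what influences adherence, and shifts are scheduled in advance so that midwives with different experience are observed. A diluted contrast could lead the study to report that time of day or experience matters less than it does. Risk group and parity, as defined, do not change at hand-over and are not affected in this way.

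**Working it through.** The protocol states no effect size or power for these comparisons, so there is no figure of its own to reproduce. The check is how far a one-label analysis would distort an assumed true contrast.

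**From the protocol.** Shift lengths: 7.30 to 14.30 = 7 h, 14.30 to 20.30 = 6 h, 20.30 to 7.30 = 11 h; 7 + 6 + 11 = 24 h. At least 150 labours.

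**Assumed, not in the documents.** Duration of observed labour, time of entry within the shift, labels by starting shift, and true scores by shift.

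**How many labours cross a hand-over.** With starts uniform over 24 h and a fixed duration D of at most 6 h, the share crossing is 3 × D / 24:
- D = 2 h: 25%
- D = 4 h: 50%, or 75 of 150
- D = 6 h: 75%, or about 113 of 150

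If all starts fall in the first 2 h of a shift, the share is 0% at 4 h and 50% at 6 h.

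**Hand check of the dilution.** For a start uniform within a shift of length L, and D no longer than L, the mean share of labour time in the starting shift is 1 − D/(2L). Take D = 4 h and true scores 0.8, 0.6, 0.4:
- Morning label: share 1 − 4/14 = 0.714; score 0.714 × 0.8 + 0.286 × 0.6 = 0.743
- Afternoon label: share 1 − 4/12 = 0.667; score 0.667 × 0.6 + 0.333 × 0.4 = 0.533
- Night label: share 1 − 4/22 = 0.818; score 0.818 × 0.4 + 0.182 × 0.8 = 0.473

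The true morning-night difference of 0.40 appears as 0.743 − 0.473 = 0.27.

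**Varying durations.** A simulation with gamma durations (SD half the mean), starting-shift labels and the same true scores, pooling observed over expected checks, gives:

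| Mean duration | Entry within shift | Morning-night difference (true 0.40) | Share retained |
|---|---|---|---|
| 4 h | first third | 0.38 | 95% |
| 6 h | first third | 0.33 | 83% |
| 4 h | uniform | 0.24 | 60% |
| 6 h | uniform | 0.16 | 40% |

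Pooling is close to what a Poisson model with an offset for expected checks estimates. With uniform entry, about 55%, 63% and 36% of morning, afternoon and night labours cross a hand-over at a 4 h mean, and 74%, 80% and 53% at 6 h.

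**A second set of true scores.** With 0.60, 0.60 and 0.40, the night-to-morning and night-to-afternoon ratios are both 0.67. For fixed durations and labels by starting shift they appear as:

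| Duration | Night/morning, uniform entry | Night/afternoon, uniform entry | Night/afternoon, entry in first 2 h |
|---|---|---|---|
| 4 h | 0.73 | 0.82 | 0.67 |
| 6 h | 0.76 | 0.91 | 0.71 |
| 8 h | 0.80 | 0.99 | 0.76 |

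With entry in the first 2 h, night/morning stays near 0.67 throughout.

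**Experience.** Assume scores of 0.6 (experienced) and 0.4 (not), a ratio of 0.67, with later staff independent of the first and half of them experienced (mean score 0.5).
- 80% of the time with the labelled staff: (0.4 × 0.8 + 0.5 × 0.2) / (0.6 × 0.8 + 0.5 × 0.2) = 0.42/0.58 = 0.72
- 60% of the time: 0.44/0.56 = 0.79

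**After the change.** In a segment that lies within one shift and one attendant's time, observed and expected checks belong to one level of each factor, so the assumed contrasts are recovered by construction.

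**The case against.** The strongest reply is that the protocol never says each labour gets one shift or one staff label, still less that the label is the starting shift. It plans to note observations by shift, supplement 1 may already capture staff and hand-over, and a statistical analysis plan could settle the coding. Dilution is also conditional. Taking the first eligible women to reach active phase, some of them already on the ward, may favour early entry. With early entry and a 4 h mean, almost the whole contrast survives. Finally, these are factor comparisons within an audit; the adherence percentages and scores of item 2 are untouched.

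Most of this stands. A reader might infer that shift and experience effects are certain to be misclassified and diluted. The documents do not support that, because the single label is an inference from the score's definition and the size rests on durations and entry times that are not given.

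A reader might also infer that the order of shifts would reverse. At a 6 h mean with uniform entry, the pooled scores do put afternoon (0.49) below night (0.53). Averaging the per-labour scores under the same assumptions gives 0.509 and 0.506, and a morning-night difference of 0.21 instead of 0.16. At a 4 h mean there is no reversal under either weighting. Reversal is possible only under a particular combination of assumptions and should not be claimed.

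The reply does not remove the structural point. The protocol itself defines the score over the whole labour and relates that score to factors that vary within it. A later rule, such as starting shift or majority shift, would still leave mixed exposure in one number.

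**Conclusion.** The point holds as a conditional one. The score is fixed over the whole labour, shift and attending staff can change within that labour, and follow-up across hand-over is intended. Any one-label-per-labour analysis of item 3 can therefore misclassify exposure and will usually dilute the contrasts.

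Under the assumptions shown, the loss in the morning-night difference runs from slight (0.40 to 0.38) to more than half (0.40 to 0.16). It is nil where no labour crosses a hand-over. The figures for experience rest on still more assumptions and are illustrative. The change is worth making because it is cheap and because hand-over times and attendants may be hard to rebuild later. It does not call the rest of the audit into question.

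**What to change.** For the shift and experience comparisons in Data analysis, item 3:

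- Split each labour at shift changes and at changes of attending staff. Count observed and expected checks per segment, assigning each expected check to the shift and attendant on duty when it falls due.
- Fit the Poisson model to the segment counts with log(expected) as offset, shift and experience as segment-level factors, and robust variance clustered at least on labour, since segments of one labour are not independent.
- Record the hand-over time and a coded attendant for each segment, unless supplement 1 already captures them. Settle this before data collection.

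The whole-labour scores and percentages in item 2 stay as they are. The cost is a few sentences in the analysis section and slightly more data entry and analysis.

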**Data collection tool**

A criteria based audit will allow us to compare current practice to the local standards. This involves structurally observing intrapartum care and determining the adherence to the local PartoMa guidelines. Therefore, a data collection is created, based upon the PartoMa guidelines and additional information on the labouring women to categorize the labours and to systematically note the observations and key events during each shift and labour is included.

**Data collection:** The gestational age (GA) will be calculated based on the available information: using the last menstrual period (LMP), ultrasound (US) findings from first trimester, fundal height measured in the first trimester or fundal height recorded on admission. This information will be collected after delivery. Please refer to supplement 1 for further details on data collected during clinical observation.

**Recordkeeping:** For now, I will solely prepare for the validation study, but photocopying the file and systematically saving it**.** Each file will have a number assigned to it and names will be covered. The timing of the recordkeeping will depend on the mode of delivery due to the loss of records at the MMH. A vaginal delivery can be recorded immediately after delivery and a CS after the morning meeting the next day latest. Method to collect data: KoBoToolbox.

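### High-risk status is said to be settled by admission, but its definition includes complications that arise or are recognised during the observed labour, so the low- versus high-risk comparison of monitoring adherence is open to bias in either direction.

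*Protocol*

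**What the plan says.** All of the following is in the protocol.

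- **Timing of risk status** (Selection of labours): "The inclusion of labours will be both high- and low-risk (as determined antenatally or on admission), both nulli- and multipara".
- **Definition, first part** (same section): "High-risk pregnancies are defined as women with a previous caesarean section, induced labour by oxytocin or having pregnancy, medical complications". The list that follows names preterm and postterm labour, PROM, meconium, maternal illness and severe bleeding.
- **Definition, last part** (same section): "foetal distress (Intrauterine foetal death, IUFD), poor progress (crossed alert line of the partogram), severe hypertensive disorder, fever or other infections".
- **Observation window** (same section): "A labour will be observed once the woman reaches active phase of labour (4 cm cervical dilatation) until complete delivery of the baby".
- **IUFD** (same section): women are excluded if "diagnosed with IUD by staff before admission by ultrasound (US". For those already under observation, "In case of an IUFD detected during labour, observations will be stopped, but data will be included in the results".
- **Key events** (same section): a separate list, which also contains bleeding and fever.
- **Use in the analysis** (Data analysis, item 3): "Influence of low-vs high-risk pregnancies, experienced vs non-experienced midwives or doctors, nulli- vs multipara, morning vs afternoon vs night shifts" and key events are related to the FHM score by a Poisson analysis. Item 2 defines that score as observations made divided by observations expected for the duration of the labour.

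Nothing in the protocol fixes a woman's risk status at the start of observation for item 3, or says how to code a woman who becomes high-risk afterwards.

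**The concern.** Objective 2 asks which factors influence adherence. For risk status to be read as such a factor, it has to come before the monitoring that it is meant to explain. The stated timing meets that condition, but the listed definition does not.

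Two mechanisms follow, with opposite signs:

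1. **Detection.** Foetal distress is recognised by checking the heart rate, and a crossed alert line by plotting the partogram. Labours that are checked more have more chance of being labelled high-risk. High-risk labours can then look better monitored even if staff never respond to risk.
2. **Poor monitoring comes first.** If sparse monitoring goes with more complications, or with later recognition of them, the high-risk group collects poorly monitored labours and looks worse monitored.

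In either case the ratio no longer answers whether staff monitor women differently because they are known to be at risk. The overlap of bleeding and fever with the key-event list adds to this, because one episode can set two explanatory factors in the same analysis.

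**Working it through.** **No stated figure to reproduce.** The protocol gives a minimum of 150 labours and no rates, effect size or power for this comparison. The check is a reading of the text followed by an illustration under assumed inputs.

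**Step 1: listed items against the stated timing**

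| Item in the high-risk list | Can it be known by the start of observation? |
|---|---|
| Previous caesarean section, preterm/postterm, maternal illness, severe hypertensive disorder | Normally yes |
| Induction by oxytocin | Mostly yes |
| PROM, meconium, fever or infection, severe bleeding, foetal distress | Sometimes; can also appear later |
| Crossed alert line | Normally no: it measures progress in active labour, and observation starts at 4 cm |
| IUFD | Mostly no: a diagnosis by ultrasound before admission excludes the woman, and detection in labour keeps her data |

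The last two rows conflict with the stated timing, as does foetal distress when it is first detected in labour. The rest of the third row may conflict.

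**Step 2: detection route, true ratio 1.00**

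Assumptions, none from the protocol: observed labour gamma-distributed with mean 6 h and SD 3 h; check rate varying between labours with CV 0.4 to 0.8, unrelated to risk; distress arising at a random time in 20% of labours and labelled only if a check follows. A share *b* of labours is high-risk at admission, independently of check rate.

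Ratio = (sum of checks / sum of expected checks) in high-risk labours ÷ the same in low-risk labours.

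| Average gap between checks | *b* = 0 | *b* = 20% | *b* = 40% |
|---|---|---|---|
| 60 min | 1.09-1.24 | 1.04-1.11 | 1.03-1.07 |
| 120 min | 1.21-1.42 | 1.09-1.17 | 1.06-1.11 |
| 180 min | 1.35-1.59 | 1.14-1.21 | 1.09-1.14 |

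Each range runs from CV 0.4 to CV 0.8. Repeat runs move the second decimal by about 0.01, so I quote 1.03-1.22 for *b* = 20-40%.

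The *b* = 0 column makes the high-risk group consist solely of detected distress, which is not the protocol's group. The dilution can be checked by hand for 180 min, CV 0.8, *b* = 20%:

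- Detected distress is 9.2% of labours, with score 1.594 relative to 1 for the rest.
- Overall mean: 1 + 0.092 × 0.594 = 1.055.
- High-risk group: 0.20 at 1.055, plus 0.80 × 0.092 = 0.0736 at 1.594.
- Mean: (0.20 × 1.055 + 0.0736 × 1.594) / 0.2736 = 0.328 / 0.2736 = 1.20.

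The simulation gives 1.21. The small gap arises because labours with detected distress are longer and weigh more in the sums.

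**Step 3: both routes with a test at 150 labours**

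A second set of assumptions: one check expected per 30 min, the same durations, mean score 0.40 with CV 0.5, 20% or 40% high-risk at admission, complication level 10%, 20% or 40%, labour-level robust variance, two-sided 0.05.

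- *Detection*: each check has a 10% or 30% chance of recognising an existing complication.
- *Poor monitoring first*: complication probability = level × exp(−(score − 0.40)/0.40).

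| Coding of risk | Ratio (truth 1.00) | Share of trials rejecting |
|---|---|---|
| Fixed at admission | 0.99-1.00 | about 5-7% |
| Ever in labour, detection | 1.03-1.18 | 6-30% |
| Ever in labour, poor monitoring first | 0.60-0.90 | 14-99% |

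For the last row, complication levels of 10%, 20% and 40% give 0.85, 0.76 and 0.60 with 20% high-risk at admission, and 0.90, 0.82 and 0.66 with 40%. In both routes the bias shrinks as fewer labours are reclassified during labour.

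**The case against.** **The timing phrase may govern the whole list.** On that reading, every item counts only if present on admission. Meconium, fever, bleeding, PROM and foetal distress can all be present then, and the protocol takes women already on the ward as well as new admissions. This is a fair reading and would remove most of the problem. However, it leaves the alert-line item nearly empty and sits badly with IUFD detected in labour, and the protocol does not say that it is meant. Two analysts could code the same woman differently.

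**The bias may be small, and its sign is unknown.** This stands. A reader might infer that high-risk labours will look better monitored, by as much as 1.35-1.59. The documents do not support that. Those values need a high-risk group made up only of detected distress, whereas the protocol's group also holds women at risk from the outset, and the opposite mechanism is just as compatible with the text.

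**Gestational age.** A reader might add preterm and postterm status to the charge, because of the gestational-age information the protocol says "This information will be collected after delivery". That describes when the data are gathered. The sources (last menstrual period, first-trimester ultrasound or fundal height, fundal height on admission) date from admission or earlier, and monitoring in labour does not produce them. At most, staff may not have known the value, which is misclassification of what they knew and not reverse causation.

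**Unseen material.** Supplement 1 and any SAP are not shown, so one cannot say that recognition times go unrecorded. The conflict between the stated timing and the definition is in the protocol text all the same.

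**Limited reach.** Risk is one of several factors in an audit, and the adherence percentages and scores in item 2 do not depend on it. This also stands.

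**Conclusion.** The point holds as a conflict between two rules in Selection of labours that carries into item 3 of Data analysis. It is clear for the crossed alert line and for foetal distress or IUFD detected in labour, and possible for meconium, fever and severe bleeding. The low- versus high-risk comparison is open to bias in either direction; that it is in fact biased, or biased upwards, cannot be concluded from the protocol.

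The size depends on how many labours become high-risk after observation starts, which is not given. With distress in 20% of labours and 20-40% high-risk at admission, detection alone gives about 1.03-1.22 in place of 1.00. The opposite route gives a ratio below 1 (0.60-0.90 under the second set of assumptions). These are illustrations and not predictions for this hospital. An unknown sign makes the result harder to interpret, not safer.

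**What to change.** 1. **Make the definition match the stated timing.** For item 3, count a labour as high-risk only if a listed condition is present and known to staff when observation starts (admission, or 4 cm if reached on the ward). This concerns the analysis variable only, not how staff assess or manage women.
2. **Handle later complications separately.** Treat a crossed alert line, foetal distress or IUFD, meconium, fever or bleeding first recognised after that point as key events or as time-dependent factors. For the latter, compare checks per expected check after recognition with those before it in the same labour, using the recorded recognition time.
3. **Remove the overlap.** Bleeding and fever should enter through one factor only: risk if present at the start, key event if recognised later.

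In the second simulation, fixing risk at admission brought the ratio back to 0.99-1.00 and the rejection rate to about 5-7%.

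The cost is a reworded definition and fewer labours in the high-risk group, hence a less precise comparison. Recognition times must be recorded for each complication if the data form does not already capture them. This should be settled before observation begins, because such times may not be recoverable afterwards; the protocol itself notes that records are lost at this hospital.
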